#### ***8.8.11 5-years post-randomisation data collection point (Follow-up)***

At the session + or – 4 weeks the 5-years post-randomisation data collection point, the CI and/or Co-CIs ask the parent to video record a conversation with the PCWS at home. The parent loads this onto a GDPR-proof

platform and labels the video recording according to the requirements. No treatment is provided during this conversation. The instructions for the video recording need to be followed.

Video analysts will score %SS and SR in the video recorded speech samples of the PCWS.

The parent is asked to complete the EQ-5D-Y proxy 1 on an electronic device (computer or smart phone) within 4 weeks before or after the data collection point. The parent is also asked to report on their child's stuttering severity based on a 10-point scale with three descriptors only and to report on the satisfaction of the PCWS's communication in everyday speaking situations based on a 9-point scale with two descriptors only. Access to the questionnaires is emailed to the parent.

## 8.9 Fidelity of implementation

Bergþórsdóttir et al. (2021) reported that clinical trials often fail to report fidelity of implementation. In treatment for preschool children who stutter, the treatment is not only implemented during the treatment session by the SLT, but also at home by the parents. It is therefore necessary to check compliance of implementation at home and during the treatment session.

In TreatPaCS, we therefore check (1) the parent's compliance and (2) the SLT's treatment delivery in the practice (for treatment fidelity). Four main components will be assessed:

- Dosage of the treatment. This includes how often the treatment was delivered, number of sessions attended, session length, length of the treatment period, length of practice time at home, number of practice times at home, ... This information is collected by the SLT when she is completing the compliance checklist.
- Adherence of the treatment. This refers to the accuracy with which the treatment was delivered. This information is known from the treatment fidelity checklists and the video recordings of the treatment sessions.
- Quality of the treatment. This refers to how well the intervention is delivered. It includes the skill with which the intervention was delivered by the parent and/or SLT, the parent's ability to engage with the child and awareness of treatment protocols. This information is collected by the SLT when she is completing the compliance checklist and the treatment fidelity checklist.
- Responsiveness to the treatment and engagement in the treatment. This is based on parent and/or child satisfaction reported by the SLT in the compliance checklists and/or direct observation of the child's behaviour as the child is the one the treatment is focused on.

Fidelity of implementation is often (and also in this trial) measured by the use of checklists, automatic recording devices, and independent observer judgment.

As mentioned previously, 20% of the PCWS the SLT will be asked to record entire treatment sessions, and to load those video recordings onto a GDPR-proof platform. The 20% correspond with two PCWS per site and will be chosen randomly with an equal distribution of the three delivered treatment approaches. The SLT will receive an automatic alert by email message if video recording is required. To avoid bias, for example, SLTs who would behave differently during the video recording compared to other treatment sessions, they are asked to video record each session during that week if they see  $\geq 3$  PCWS in the study at that time or all treatment sessions during 3 weeks if they see  $< 3$  PCWS at that time. The instructions for the video recording the treatment session need to be followed (these are different instructions than for video recording the speech sample).

### **8.9.1 Parent treatment compliance**

SLTs use a compliance checklist during each treatment session to assess treatment compliance at home for each type of treatment (see Appendix 9). The checklist mainly includes questions about treatment implementation (dosage and adherence). During the treatment session, the SLT asks the parent to demonstrate or observes how s/he implements the treatment at home. The observation of this parent demonstration provides an answer to the aspects of quality of treatment implementation and responsiveness to the treatment. The presence of at least 80% of treatment aspects defines acceptable parent treatment compliance. The SLT uses an electronic checklist or a paper-based checklist that s/he keeps in the PCWS' speech-language therapy file. The SLT uploads the information in REDCap at each data collection point.

### **8.9.2 SLT treatment fidelity**

To assess SLTs' treatment fidelity to dosage and adherence, automatic recorded data are used. In addition, SLTs make a video recording of their treatment session with the PCWS and parent 1, 3, 6 and 12 months post-randomisation. Instructions for the video recording are provided.

The videos are assessed by two unblinded video analysts who have expertise in the three types of treatments. The French-speaking video analyst watches the videos of the treatment delivered in French; the Dutch-speaking video analyst watches the videos of the treatment delivered in Dutch. A treatment fidelity checklist consisting of treatment aspects related to quality of treatment implementation and responsiveness to the treatment is used (see Appendix 9). In case inconsistencies are observed, the second video analyst, independent of the TreatPaCS trial, watches the video recording as well. The presence of at least 80% of treatment aspects defines acceptable SLT treatment fidelity.

The unblinded video analysts won't be scoring the other video recordings (speech samples) for %SS and SR.

### 8.9.3 Video analysis: Rating of %SS and SR

The video analyst coordinator organises the video analysis process. The video analysts look at the videos that are uploaded onto a GDPR-proof platform to calculate %SS and assign a SR to the two video recordings (one from home and one from the treatment session) at each data collection point. An average of the two scores will be taken as outcome measure. Success of the intervention is frequently defined in terms of achieving <1% SS. To achieve such a low average, one must have very low scores in both speech samples (home and during the treatment sessions), so averaging the % SS is routine practice in the standard clinical care.

The video analysts will be able to access the video recordings without knowing which treatment approach the PCWS is receiving/has received. A list of the videos of the French-speaking PCWS (for the French-speaking video analysts) and a list of the videos of the Dutch-speaking PCWS (for the Dutch-speaking video analysts) will be generated without information about the treatment arm and the time on which the video is recorded. In each list, 5% of the video recordings will re-appear as those are intended to be rated by two video analysts to establish the interrater agreement (see further for detail about the interrater agreement analysis). This 10% of videos is clearly indicated on the list. The video analysis will commence 6 months after the start of recruitment. This 6-month waiting time is included to avoid bias for the baseline video recordings.

If a PCWS speaks another language than Dutch, French or English, the research team will use their network to search for a native speaker of the language spoken by the PCWS and parent. This person will be invited to help the video analyst with scoring the video.

Standardisation of the video analysts will be guaranteed by a manual and by a training in which three video recorded speech samples (other than TreatPaCS-videos) will be scored together with all video analysts for %SS and SR.

Quality of the ratings will be assured by an evaluation of five video samples of French-speaking PCWS performed by the French-speaking video analysts and five video samples of Dutch-speaking PCWS performed by the Dutch-speaking video analysts. In a meeting they will discuss the stuttering moments and come to a consensus.

For %SS, clear instructions will be provided, including:

- Only the stuttering behaviour is counted; not the normal disfluencies (a more detailed stuttering type is not to be considered in this judgement). The stuttering behaviour may appear with or without tension.
- When more than one stuttering behaviour appear on one syllable (for example, a block and a repetition such as: ... [tension, no sound] ... I-I-I-I want ... (= block, sound repetition) it is counted as one as it occurs on one syllable.

- For counting the total number of syllables, clear instructions are given for what to include in the counting and what not. For example, isolated /yes/ or /no/ are not to be counted as a syllable.

For SR, tools are provided, including:

- A visual scoring chart such as the one used in the LP (Onslow et al., 2021) will be provided with 0 = no stuttering, 1 = extremely mild stuttering and 9 = extremely severe stuttering.
- Five supporting questions will be provided to help the video analysts assign the SR score:

| STUTTERING SEVERITY SCORES                            |                            |                                                                                                      |                                                              |                                                                   |                                                                    |
|-------------------------------------------------------|----------------------------|------------------------------------------------------------------------------------------------------|--------------------------------------------------------------|-------------------------------------------------------------------|--------------------------------------------------------------------|
|                                                       | Score 0                    | Score 1-2                                                                                            | Score 3, 4 and 5                                             | Score 6, 7 and 8                                                  | Score 9                                                            |
| Severity of stuttering                         | No stuttering              | Extremely mild/mild                                                                                  | Moderate                                                     | Severe                                                            | Extremely severe                                                   |
| What types of stutters appear and how often?   | No stutters                | Very occasional/ occasional repetitions and/or very occasional and brief prolongations and/or blocks | More frequent repetitions and/or prolongations and/or blocks | Frequent repetitions and/or prolongations and/or blocks           | Frequent and severe repetitions and/or prolongations and/or blocks |
| How does the child get his/her message across? | Gets message across easily | Gets messages across easily/ quite easily                                                            | May take some time and effort to get message across          | Takes lots of time and sometimes cannot get message across at all | Usually cannot get message across at all                           |
| Does the child's speech sound effortful?       | No                         | No                                                                                                   | Sometimes                                                    | Most of the time                                                  | Almost always                                                      |
| Would another person notice the stuttering?    | There is no stuttering     | Probably not/ Probably                                                                               | Certainly                                                    | Certainly; likely to feel uncomfortable about it                  | Certainly; will frequently feel uncomfortable about it             |

A manual with clear guidelines will be provided to the video analysts in which it is described how they should count the disfluencies. Also, a clear description of how to assign SR will be given. This manual will be added to the Trial Master File.

Videos of PCWS who speak a language other than Dutch, French or English will be viewed by a video analyst and a person who speaks the language of the child. The video analyst can ask the speaker of the language for advice in case ambiguous disfluencies are present in the speech sample.

Inter-rater agreement will be computed for 10% of the videos. Inter-rater agreement will be calculated with an Intraclass Correlation Coefficient (ICC).

|                                                                        | Pre-treatment             |                    |          | Treatment (Tx)                                                        |                                                                                                                                  |                                               |                                                |                                                       | Follow-up                          |                                    |
|------------------------------------------------------------------------|---------------------------|--------------------|----------|-----------------------------------------------------------------------|----------------------------------------------------------------------------------------------------------------------------------|-----------------------------------------------|------------------------------------------------|-------------------------------------------------------|------------------------------------|------------------------------------|
|                                                                        | Screening at SLT practice | Active monitoring* | Baseline | Tx at 3 months post-randomisation +/- 2 weeks                         | Tx at 6 months post-randomisation +/- 2 weeks                                                                                    | Tx at 9 months post-randomisation +/- 2 weeks | Tx at 12 months post-randomisation +/- 2 weeks | Tx at 18 months post-randomisation +/- 2 weeks | 2yr post-randomisation +/- 4 weeks | 5yr post-randomisation +/- 4 weeks |
|                                                                        | (Day -92 - Day 0)         | (if needed)        | (Day 1)  | (weekly-twice weekly interval with previous Tx session a ) | (interval: weekly-twice weekly interval with previous Tx session a or greater interval if Tx is in Maintenance Phase) |                                               |                                                |                                                       |                                    |                                    |
| Informed consent form signed by one parent                             | x                         |                    |          |                                                                       |                                                                                                                                  |                                               |                                                |                                                       |                                    |                                    |
| Information form for the child signed by the SLT                       |                           |                    | x        |                                                                       |                                                                                                                                  |                                               |                                                |                                                       |                                    |                                    |
| Eligibility assessment                                                 | x                         |                    |          |                                                                       |                                                                                                                                  |                                               |                                                |                                                       |                                    |                                    |
| Anamnesis (time since onset, gender, ...)                              | x                         |                    |          |                                                                       |                                                                                                                                  |                                               |                                                |                                                       |                                    |                                    |
| Active monitoring data                                                 |                           |                    | (x)      |                                                                       |                                                                                                                                  |                                               |                                                |                                                       |                                    |                                    |
| Randomisation                                                          |                           |                    | x        |                                                                       |                                                                                                                                  |                                               |                                                |                                                       |                                    |                                    |
| Stuttering severity by SLT (SSI-4, TVS-NL/TSB-NL)                      | x                         |                    | (x)      |                                                                       |                                                                                                                                  |                                               |                                                |                                                       |                                    |                                    |
| Treatment depending on arm                                             |                           |                    | x        | x                                                                     | x                                                                                                                                | x                                             | x                                              | x                                              | (x)                                |                                    |
| Speech sample from Tx session                                          |                           |                    | x        | x                                                                     | x                                                                                                                                | x                                             | x                                              | x                                              | (x)                                |                                    |
| Speech sample from home                                                |                           |                    | x        | x                                                                     | x                                                                                                                                | x                                             | x                                              | x                                              | x                                  | x                                  |
| %SS **                                                                 |                           |                    | x        | x                                                                     | x                                                                                                                                | x                                             | x                                              | x                                              | x                                  | x                                  |
| SR **                                                                  |                           |                    | x        | x                                                                     | x                                                                                                                                | x                                             | x                                              | x                                              | x                                  | x                                  |
| KiddyCAT                                                               |                           |                    | x        |                                                                       |                                                                                                                                  |                                               |                                                | x                                              |                                    |                                    |
| Treatment date & duration                                              |                           |                    |          | x                                                                     | x                                                                                                                                | x                                             | x                                              | x                                              | (x)                                |                                    |
| Compliance & treatment fidelity ®                           |                           |                    |          | x                                                                     | x                                                                                                                                | x                                             | x                                              | x                                              | (x)                                |                                    |
| QOL (EQ-5D-Y proxy 1)                                                  |                           |                    | x        | x                                                                     |                                                                                                                                  | x                                             |                                                | x                                              | x                                  | x                                  |
| CBQ-short version                                                      |                           |                    | x        |                                                                       |                                                                                                                                  |                                               |                                                |                                                       |                                    |                                    |
| ISPP-questionnaire                                                     |                           |                    | x        | x                                                                     |                                                                                                                                  | x                                             |                                                | x                                              |                                    |                                    |
| Parent report about stuttering and satisfaction everyday communication |                           |                    | x        | x                                                                     | x                                                                                                                                | x                                             | x                                              | x                                              | x                                  | x                                  |
| Drop-out/leave the allocated treatment arm                             |                           |                    |          | x                                                                     | x                                                                                                                                | x                                             | x                                              | x                                              | (x)                                |                                    |
| Relapse reporting and relapse management                               |                           |                    |          |                                                                       | x*                                                                                                                               | x*                                            | x*                                             | x                                              | (x)                                |                                    |
| Risk assessment                                                        |                           |                    |          | x                                                                     | x                                                                                                                                | x                                             | x                                              | x                                              | x                                  |                                    |

Tx = Treatment; %SS = Percentage syllables stuttered; SR = Severity Rating; CAT = Communication Attitude Test; QOL = Quality of Life; CBQ = Children's Behaviour Questionnaire; ISPP = Impact of Stuttering on Preschoolers and Parents; \*: if applicable, that is, if treatment is not initiated straight away; \* if applicable, that is, if the child is in Maintenance Phase. (x) if applicable, that is, if the child is still seeing the SLT; Underlined & bold (18 months post-randomisation) = primary end point; \*\* performed by the video analysts; a depending on the treatment arm; ® Parent compliance and treatment fidelity checklists are completed for each treatment session; ® Treatment fidelity is also evaluated based on of video that is recorded for 20% of the PCWS (entire treatment session) at 1-, 3-, 6- and 12-months post-randomisation.

Figure 3. Overview of measurements in TreatPaCS

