## Trial Management Group

The Trial Management Group meets regularly and are responsible for the daily management of the study. During their meetings, they discuss overall progression of the study, practical hurdles that are reported by participating SLTs, questions coming from the SLTs, database issues and all other minor practical issues that demand quick resolution. The Trial Management Group is composed of CI, Co-Cis, PM, Trial Statistician, Data Manager, CTC UZ-Antwerpen support and when relevant, other members with specific interests such as the Field Monitors or the Video Analysts. If important or relevant items for the SLTs were discussed, the respective SLT or – if relevant – all SLTs will receive this information through e-mail. Minutes from every meeting as well as communication with the SLT(s) will be available in the Trial Master File.

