## **8.4 Blinding**

The participating SLTs, PCWS and their parents are not blinded to the treatment approaches that they deliver/receive. The three treatment approaches (Mini-KIDS, SCBT and the LP) use distinct techniques. Blinding is thus impossible.

The video analysts who are scoring %SS and SR are blinded to the treatment approaches that the PCWS receives. In the unlikely event that a video analyst is unblinded for the treatment that is delivered by the SLT in a video, for example if the video analyst recognises the name of a PCWS in the video because it was mentioned by the SLT during a SLT-RCT committee meeting, the video analyst will stop rating the video and will transfer the video to another video analyst who is blinded to the treatment.

Two video analysts are not blinded and will assess the French and Dutch video recordings for treatment fidelity.

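### The videos used to measure inter-rater agreement are marked for the raters, their share is given as both 5% and 10%, and the blinded raters are not kept out of meetings with child-level content

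*Protocol*

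**What the plan says.** Section 8.9.3 describes how %SS and SR are scored. One list of videos per language goes to the analysts of that language. For the Dutch side, "a list of the videos of the Dutch-speaking PCWS (for the Dutch-speaking video analysts) will be generated without information about the treatment arm"; the French side is parallel, and recording time is withheld as well. On double rating it says: "In each list, 5% of the video recordings will re-appear as those are intended to be rated by two video analysts". It then says: "This 10% of videos is clearly indicated on the list". The paragraph on the agreement statistic, later in the same section, says: "Inter-rater agreement will be computed for 10% of the videos". The statistic is an ICC.

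On blinding, section 8.4 states that SLTs, parents and children know the treatment and that the analysts scoring %SS and SR do not. Its example of accidental unblinding is an analyst who "recognises the name of a PCWS in the video because it was mentioned by the SLT during a SLT-RCT committee meeting". In that case the analyst stops and passes the video to another blinded analyst (8.4, 8.5). The descriptions of the Dutch- and French-speaking SLT-RCT committees list a Co-CI, the participating SLTs and the CI, and no video analysts. The Trial Management Group, by contrast, may include, when relevant, "other members with specific interests such as the Field Monitors or the Video Analysts". Sections 10.2.2 and 10.3 give that group the decision on each reported adverse event, which can include leaving the allocated arm.

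**The concern.** An agreement study on a sample of ratings is useful only if the sample is rated like the rest. When the sample is marked on the raters' own list, they know which scores will be compared and can take more care with them. %SS leaves room for this: the analyst must separate stuttering from normal disfluency, and 8.9.3 itself foresees ambiguous cases. The protocol takes this kind of effect seriously elsewhere. Section 8.8.4 has SLTs record every session over a period so that they do not behave differently in the sessions that are checked.

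The 5% and 10% figures cannot both be the share of distinct videos with two ratings, and the choice changes the size of the reliability sample by a factor of two.

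Blinding matters more than usual here because the rater is the only blinded person in the chain that produces the primary endpoint. A rater who attends a meeting on a particular child's adverse event or change of arm could learn the allocation. The hand-over rule works only if that rater recognises the child and reports it.

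**Working it through.** **1. Can 5% and 10% be the same quantity?** Let V be the number of distinct videos, split into V_F French and V_D Dutch.

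- 5% of each list: 0.05·V_F + 0.05·V_D = 0.05·V. Adding the two language lists does not make 10%.
- Originals plus repeats as list entries: (0.05·V + 0.05·V) / 1.05·V = 0.10/1.05 = 9.5%. This is the only reading close to 10%. It counts entries, whereas the later paragraph says 10% of the videos.

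The stated 10% is therefore not reproduced from the stated 5%.

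**2. What the difference amounts to.** Inputs are 249 children (11.1) and two videos per child per data point (8.9.3), assuming no missing videos. The data points are baseline, 3, 6, 9, 12 and 18 months, and 2 years.

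| Span | Videos | 5% | 10% |
|---|---|---|---|
| Baseline to 18 months (6 points) | 249 × 6 × 2 = 2,988 | 149 | 299 |
| Baseline to 2 years (7 points) | 249 × 7 × 2 = 3,486 | 174 | 349 |
| 18 months only, even sampling | 249 × 2 = 498 | 25 | 50 |

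These are upper limits, since dropout and missing recordings reduce them.

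**3. Effect on the precision of the ICC.** The protocol gives no expected ICC, so values of 0.7, 0.8 and 0.9 are assumed. For two raters, F = (1 + r)/(1 − r). The approximate 95% limits are (F/q − 1)/(F/q + 1) and (F·q − 1)/(F·q + 1), where q is the 97.5% point of the F distribution on n − 1 and n − 1 degrees of freedom. At r = 0.8, F = 1.8/0.2 = 9.

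| Assumed ICC | n = 25 | n = 50 | n = 149 | n = 299 |
|---|---|---|---|---|
| 0.7 | 0.43–0.86 | 0.53–0.82 | 0.61–0.77 | 0.64–0.75 |
| 0.8 | 0.60–0.91 | 0.67–0.88 | 0.73–0.85 | 0.76–0.84 |
| 0.9 | 0.79–0.96 | 0.83–0.94 | 0.86–0.93 | 0.88–0.92 |

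Pooled over visits, either share gives a usable interval. At 18 months alone, the primary time point, 25 videos give a wide one.

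**4. Effect of marking.** No size can be computed. If marking increases care, agreement on the marked videos overstates agreement on the unmarked 90% (at a 10% share) to 95% (at 5%). If it does not, there is no effect. The design cannot distinguish the two.

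**5. Meetings, set side by side.**

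- SLT-RCT committees: analysts are not listed as members, yet the example in 8.4 has an analyst recognising a name that an SLT mentioned there. The two places do not fit together.
- Trial Management Group: Video Analysts are admitted without saying which. Sections 8.4 and 8.9.2 describe two kinds, the blinded raters and two unblinded fidelity analysts who do not score %SS or SR. The wording covers both.

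**The case against.** The strongest reply is that nothing here shows a biased result. A reader might infer that agreement is inflated. The documents do not support that: they give no evidence that raters behave differently on marked videos, and the second rating comes from a different analyst who is not said to see the first score. Marking may also serve a purpose, because a video that re-appears on a shared list has to go to someone else. The ICC enters neither the sample size in 11.1 nor the primary analysis in 11.3.2.

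A reader might also infer that blinded raters sit in SLT-RCT meetings. The membership lists say otherwise, and 8.4 calls its example unlikely. The reference to Video Analysts in the Trial Management Group could mean only the fidelity analysts.

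There are real safeguards. Arm and recording time are left off the lists. Rating starts 6 months after recruitment begins. No treatment is given in the recorded sample. Full names are barred from the videos and from exchanges between SLTs and the research team (14.7). Raters have a manual, joint training and consensus samples.

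Much of this stands. It limits the point to a possible overestimate and a possible leak. It does not remove the point. The coordinator can route a repeat to a second analyst without marking it for either rater. First names may still be heard on the videos, according to 14.7. The group that decides on individual children is open to Video Analysts without restriction.

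**Conclusion.** The point holds in a limited form. The double-rating share contradicts itself within 8.9.3, at about 174 versus 349 of up to 3,486 videos to 2 years and about 25 versus 50 of 498 at 18 months. These counts assume full follow-up and, for 18 months, even sampling over visits. The reliability sample is marked for those whose reliability it measures, so the ICC may overestimate agreement for the unmarked videos that make up most of the primary endpoint data. The size of any overestimate is unknown.

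The blinding gap is one of wording: Trial Management Group attendance is not restricted to unblinded analysts, and 8.4 does not match the SLT-RCT membership. It would be going too far to conclude that blinding has failed or that %SS at 18 months is biased. A leak would need a rater to attend, recognise the child, recall the arm and not report it. The sample size is unaffected. The change is worth making because it is cheap and protects the only blinded step in the primary endpoint.

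**What to change.** 1. In 8.9.3, state one share, defined as the percentage of distinct videos rated by two analysts, and use it throughout. If 10% is the plan, this is a wording change. If 5% was meant, moving to 10% adds up to 349 − 174 = 175 ratings over 2 years.
2. Have the video analyst coordinator assign each repeat to a second analyst without marking it for either rater. Draw the repeats at random within language, with 18-month videos guaranteed in the sample. If marking is kept, say why it is needed.
3. State that analysts who score %SS and SR do not attend SLT-RCT meetings or Trial Management Group items with child- or arm-level content. In the Trial Management Group description, replace the general reference to Video Analysts with the unblinded fidelity analysts or the coordinator. Reconcile the committee descriptions with the example in 8.4.

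Apart from any extra ratings under item 1, the cost is wording in 8.4, 8.9.3 and the committee descriptions, plus some work for the coordinator.

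Repeating the primary analysis without videos whose arm the rater guessed correctly is not recommended. It selects on a post-randomisation variable that may depend on the child's fluency. It would also leave some children with one of the two samples that the endpoint averages.
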